**Flowchart selection, inclusion, intervention and measurement.**

### Inclusion and exclusion criteria

We will include participants who are at risk for developing postpartum depression. More specifically, we will include participants of 18 years and older, who are pregnant but are at least 10 weeks before the expected delivery date, and have at least mild symptoms of depression or anxiety. Symptoms of depression are measured with the Center for Epidemiological Studies Depression scale (CES-D) and symptoms of anxiety with the Hospital Anxiety and Depression Scale- Anxiety subscale (HADS-A)
[20, 21]. Patients are eligible if they score at least 16 on the CESD and/or 8 on the HADS-A. Participants who indicate that they either intend to harm themselves or want to attempt suicide (as assessed by one question of the Web Screening Questionnaire (WSQ)
[22]) will be excluded. They are advised to consult their general practitioner to obtain more tailored care. Receiving psychiatric treatment including psychotherapy or the use of psychopharmacological agents such as antidepressants is allowed. Any additional treatments will be monitored through patients self-report at the end of study.

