### Instruments

#### Primary outcomes

**Depressive symptoms** We will use the Dutch version of the CES-D to measure symptoms of depression
[20]. This questionnaire has 20 self-rated items, each scored 0–3. The total score range is 0 (no depressive symptoms) to 60 (high number of depressive symptoms). The validity has been tested in different populations. Scores of 16 and higher represent a clinically significant level of depressive symptoms with a sensitivity of 0.82-1.00 and a specificity of 0.69-0.88
[26, 27] and is chosen as an inclusion criterion.

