### Sample size and statistical analysis

Analyses will be conducted according to intention-to-treat as well as per protocol principle. To study differences between the conditions we will use linear mixed models with symptoms of depression and anxiety as dependent variables, time indicators and treatment dummy as predictors, since these types of models account for drop out over time. We will compute both within group effect sizes and between group effect sizes. The within group effect sizes are standardized differences of (predicted) means of the follow up scores and baseline scores. The between group effect sizes concern differences between within group effect sizes. We assume that the between group effect size (Cohen’s d) at the end of the study will be at least 0.40, because this has been demonstrated in a meta-analysis on supported internet treatments in general
[13] and in previous studies using the same problem solving internet treatment
[19, 25]. Using an alpha of 0.05 (two-tailed), a statistical power (1-bèta) of 0.80, and an attrition rate of 30%
[19] we need 143 respondents in each arm. All analyses will be conducted using SPSS for Windows, version 20 and STATA 10.0.

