### Economic analysis

The economic analyses are undertaken from a societal perspective, taking into account intervention costs, direct medical costs, direct non-medical costs and indirect costs during the study period
[38]. Indirect costs refer to lost resources and opportunities resulting from the disease. We will assess health service uptake and production losses at T0, T1, T2 and T3 based on the TIC-P. Full economic costs due to care utilisation and production losses are obtained from the national manual for cost prices in the health care sector. The intervention costs concern the costs related to the internet application, the advertisement and the training/salary of the coaches. Indirect costs include production losses both in paid labour and in the domestic sphere. In addition, both costs due to work loss and work cut-back are assessed, as work cut-back in patients with affective symptoms may be substantial. To calculate indirect costs the friction cost method is used, thereby taking the replacement of sick employees into account, resulting in more conservative cost estimates than the human capital approach. As the timeframe used in the present study is relatively short, costs are not discounted nor corrected for inflation.

To account for the possible non-normality of the cost data, sample errors and 95% confidence intervals are based on resampling methods (bootstrapping) using 2,500 replications.

A cost-effectiveness analysis assesses the costs per recovered patient
[39]. Quality of life is assessed at each assessment point with the Euroqol, and the average quality of life during the study period is calculated.

A cost-utility analysis is similar to a cost effective study, but assesses the incremental costs per QALY gained during the study period (instead of the incremental costs per recovery).

We will report the incremental cost-effectiveness ratio. The Incremental cost-effectiveness ratio (ICER) is the ratio between the difference in costs (between experimental and control condition) and the difference in effects (between experimental and control condition), where costs is the average annual per capita cost and effects is the percentage of participants that recovered from their depression.

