## Discussion

The aim of this study is to investigate the effectiveness of an internet-based self-help intervention on depressive and anxiety symptoms in pregnancy. Furthermore we investigate the effects on pregnancy outcome. Through a calculation of costs and quality of life gains an indication can be given on the cost effectiveness of the intervention. This study has several limitations.

First not all women have access to the internet. This might be especially true for those with increased vulnerability for affective symptomatology during pregnancy such as social disadvantaged women in particular those with illiteracy, low educational level and low income. However especially in Western countries internet is broadly available and therefore this intervention is widely accessible during pregnancy.

Second, drop out rate may be high in the non intervention group due to lack of motivation. In order to counter this, therapy is offered at a later stage, 6 weeks post delivery.

A third limitation is the use of self rating instruments only. However since this intervention is aimed at affective symptoms and not at affective disorders a formal diagnosis seems not necessary.

The strength of the study is that we examine a short practical intervention for a specific group with mild to severe affective symptoms, which has proven to be (cost) effective in other populations. The broad inclusion and the use of the internet will allow us to create a high external validity. Furthermore the study is not only aimed at depressive, but also at anxiety symptoms, which is a common, but often neglected symptom in pregnancy and postpartum.

In case effectiveness is proven we will be able to offer an effective treatment of affective symptoms in pregnancy and their complications, reach many women and making therapy easier accessible.

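### The cost-per-recovery ratio counts only recovery from depression, although women may enter on anxiety alone with a CES-D score below the article's own depression threshold

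*Protocol article*

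**What the plan says.** All places are in the protocol article.

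- **Inclusion and exclusion criteria.** Participants must "have at least mild symptoms of depression or anxiety". The operational rule is: "Patients are eligible if they score at least 16 on the CESD and/or 8 on the HADS-A". HADS-A of 8 or more with CES-D below 16 is therefore enough for entry.
- **Primary outcomes.** The CES-D threshold has a stated meaning: "Scores of 16 and higher represent a clinically significant level of depressive symptoms".
- **Economic analysis.** "A cost-effectiveness analysis assesses the costs per recovered patient". The ratio is then spelled out: costs are an annual average per head, and "effects is the percentage of participants that recovered from their depression". The percentage is not limited to women above the CES-D threshold at baseline, and there is no counterpart for anxiety. A separate cost-utility analysis uses QALYs from the Euroqol.
- **Discussion.** Anxiety is presented as a target and a strength: "the study is not only aimed at depressive, but also at anxiety symptoms".
- **Table 1.** CES-D and HADS are both collected at T0, T1, T2 and T3.

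**The concern.** The entry rule and the effect measure describe different populations. A woman who enters on HADS-A alone has, by the article's own threshold, no clinically significant level of depressive symptoms from which to recover. She still incurs intervention costs, and her health care use is counted whatever its cause, so she is on the cost side of the ratio in full. On the effect side her place depends on a coding choice, and the outcome for which she was enrolled is not counted.

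At stake are the recovery percentages, the cost per recovery, and the bootstrapped plane and acceptability curve built on that ratio. If the coding is settled only at analysis, it may be chosen with the results in view.

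**Working it through.** **The plan's own figures.** The article gives no number for this ratio: no anxiety-only share, recovery rate or cost difference. Its one reproducible figure is the sample size. With d = 0.40, two-sided alpha 0.05 and power 0.80, the t-test solution is 99.08 per arm, rounded up to 100. Then 100 / 0.70 = 142.9, rounded up to 143, as stated. That figure does not depend on the definition of recovery.

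**Three ways to read the effect measure for a woman with HADS-A of at least 8 and CES-D below 16 at T0**

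1. She counts as not recovered, because she had no depression to recover from. She can never add to the effect.
2. Recovery means CES-D below 16 at follow-up. She meets the definition before treatment starts.
3. The percentage is taken only among women with CES-D of at least 16 at baseline. The effect then comes from a subset, while the per-head cost carries no such restriction, so the two sides of the ratio describe different women.

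None of the three gives an effect that fits the randomised population as the text stands.

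**Size, by illustration**

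Let f be the share entering on HADS-A only, D the recovery difference between arms among women with baseline CES-D of at least 16, and A the difference between arms among the anxiety-only women. Then

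all-participant difference = (1 − f) × D + f × A.

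Under reading 1, A = 0. Under reading 2, A = 0 if equal proportions in both arms stay below 16. If incremental cost per woman is also the same in both groups, cost per recovery over all women, relative to that among women with baseline CES-D of at least 16, is 1 / (1 − f). This factor does not depend on D.

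Assume recovery of 50% versus 35%, so D = 15 points:

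| f (assumed) | All-participant difference | Cost-per-recovery factor |
|---|---|---|
| 10% | 0.90 × 15 = 13.5 points | 1 / 0.90 = 1.11 |
| 20% | 0.80 × 15 = 12 points | 1 / 0.80 = 1.25 |
| 30% | 0.70 × 15 = 10.5 points | 1 / 0.70 = 1.43 |

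**Effect on the reported percentages.** At f = 30%:

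- Reading 1: 0.70 × 50 = 35% versus 0.70 × 35 = 24.5%.
- Reading 2, if all these women stay below 16: 35 + 30 = 65% versus 24.5 + 30 = 54.5%.

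The difference is 10.5 points both times, but the levels move by 30 points through coding alone.

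**Sensitivity to A = 0.** Under reading 2, suppose f = 20% and 85% versus 75% of the anxiety-only women stay below 16, so A = 10 points. The difference is 0.80 × 15 + 0.20 × 10 = 14 points, and the factor is 15 / 14 = 1.07 instead of 1.25.

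**The case against.** Three stronger conclusions are tempting, and the article does not support them.

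- **That benefit on anxiety is ignored.** A reader might infer this for the whole evaluation. The cost-utility analysis covers every woman, its Euroqol has a dimension for depression and anxiety, and anxiety is a dependent variable in the mixed models. The gap is confined to the cost-per-recovery ratio.
- **That the ratio is inflated by 1.11 to 1.43.** Incremental cost over all women divided by incremental depression recoveries over all women is a coherent quantity for the population offered the intervention. The factors compare it with a subgroup ratio and hold only under the stated assumptions. The trial also enrols women at risk of postpartum depression, so some anxiety-only women could rise above CES-D 16 at rates that differ by arm. If few women enter on anxiety alone, the effect is small.
- **That recovery is meaningless for these women because they are not depressed.** CES-D below 16 is a self-report screening result and no diagnostic interview is done. All that can be said is that they start below the article's own threshold.

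It can also be argued that recovery from one's depression implies a restriction to women who had it, and that instrument, cut-off and time point belong in a fuller document. The second argument stands as far as missing detail goes, and that absence is not the point here. The first leads to reading 3 and its mismatch with unrestricted costs. The conflict between a stated entry rule and a stated effect measure remains.

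**Conclusion.** The point holds for the cost-per-recovery ratio and what is derived from it. The stated effect measure does not fit the women randomised: those entering on HADS-A alone are either recovered at T0 or unable to recover, and remission of their anxiety does not count. The primary mixed models, the sample size and the cost-per-QALY analysis are untouched, and economic costs are a secondary outcome. This is therefore worth correcting before analysis but is no threat to the main result.

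The size cannot be computed from the article. The range of 1.11 to 1.43 rests on three assumptions: an anxiety-only share of 10% to 30%, no difference between arms among these women, and equal incremental cost per woman. It illustrates what could happen and does not estimate a bias.

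**What to change.** Define recovery for every randomised woman as CES-D below 16 and HADS-A below 8 at one prespecified follow-up such as T3. This is the exact complement of the entry rule, so nobody is recovered at baseline, everyone can recover, and the intention-to-treat population is kept. T2 would suit less well, because women starting after 24 weeks of pregnancy are not assessed then.

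Report depression recovery separately among women with CES-D of at least 16 at T0, with costs taken from the same women. The subset is defined before randomisation, so the comparison between arms stays a randomised one.

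The cost is one definition in the Economic analysis section. Both scales are already collected at T0 and T3, and the cost questionnaire at every assessment. The downside is that the composite is stricter: a woman whose depression remits but who newly reaches 8 on the HADS-A counts as not recovered. The separate depression analysis shows what the composite hides in such cases.

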We will report the ICER, the scatter of the bootstrapped ICERs on the ICER plane and the ICER acceptability curve for the probability that the intervention dominates care as usual for a series of willingness-to-pay ceilings. Use will be made of the pertinent guidelines for health economic evaluation.

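### The acceptability curve is worded as a probability of dominance, which does not vary with the willingness-to-pay ceiling and is only a lower bound on the probability of cost-effectiveness (minor correction)

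*Protocol article*

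**What the plan says.** The last part of the Economic analysis section lists three outputs: the ICER, the scatter of bootstrapped ICERs on the plane, and "the ICER acceptability curve for the probability that the intervention dominates care as usual for a series of willingness-to-pay ceilings". It then adds: "Use will be made of the pertinent guidelines for health economic evaluation".

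Earlier, the same section defines the ICER as the between-arm cost difference divided by the between-arm effect difference, where "effects is the percentage of participants that recovered from their depression". It also plans a cost-utility analysis that "assesses the incremental costs per QALY gained during the study period". Uncertainty comes from "resampling methods (bootstrapping) using 2,500 replications".

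The article gives no net-benefit rule, does not say what being cost-effective at a given ceiling means, and gives 'dominates' no special meaning.

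**The concern.** An acceptability curve shows how the probability that an intervention is worth its cost changes with what the payer will spend per unit of effect. Dominance is a different event: better effect and lower cost together. It is one quadrant of the plane, and its share of replicates is the same whatever the payer will spend. The sentence therefore pairs a quantity that cannot vary with the ceiling with an axis made of ceilings.

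The cost-effectiveness question is the third numbered aim in the Background. If the sentence were followed to the letter, an intervention that works but costs somewhat more would get the same probability at every ceiling, and that figure would be too low. The setting makes this plausible: the intervention arm carries costs for the application, advertising and coaches, and the comparator is a waiting list with usual care.

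**Working it through.** **The plan's own figures.** The article states no value for the curve, so there is none to reproduce. Its one computed design figure, 143 per arm, does reproduce: a two-sample t-test with d = 0.40, two-sided alpha 0.05 and power 0.80 needs 99.08, rounded up to 100 per arm, and 100/0.70 = 142.9, rounded up to 143. This point does not depend on it.

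**Algebra (no outside figure needed).** Let dE be the effect difference, dC the cost difference and λ ≥ 0 the ceiling.

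- Dominance: dE > 0 and dC < 0. There is no λ in it, so its probability is constant.
- Cost-effective at λ: λ·dE − dC > 0.
- If dE > 0 and dC < 0, then λ·dE ≥ 0 and −dC > 0, so the sum is positive. Hence P(dominance) ≤ P(λ·dE − dC > 0) at every λ ≥ 0.
- The gap consists of replicates that are more effective and more costly with dC < λ·dE, plus replicates that are less effective and cheaper with a saving large enough to offset the loss. At λ = 0 only the second group counts. As λ rises, the first group takes over.

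**Size (all inputs assumed).** Effects are taken as recovery proportions, so λ is in euro per recovery.

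*Set A, closed form.* dE has mean 0.12 and SE 0.065; dC has SE 300 euro; dE and dC are independent. With mean dC = 300:

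- P(dominance) = Φ(0.12/0.065) × Φ(−300/300) = 0.968 × 0.159 = 0.15.
- λ = 2,500: the mean net benefit is 2,500 × 0.12 − 300 = 0, so the probability is 0.50.
- λ = 5,000: the mean is 300 and the SD is √(325² + 300²) = 442, so Φ(0.68) = 0.75.
- λ = 10,000: the mean is 900 and the SD is √(650² + 300²) = 716, so Φ(1.26) = 0.90.

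| Mean dC (euro) | P(dominance), any λ | λ = 2,500 | λ = 5,000 | λ = 10,000 |
|---|---|---|---|---|
| 0 | 0.48 | 0.81 | 0.91 | 0.95 |
| 300 | 0.15 | 0.50 | 0.75 | 0.90 |
| 500 | 0.05 | 0.28 | 0.59 | 0.84 |

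*Set B, 2,500 simulated draws per row.* SE of dE 0.07, SE of dC 600 euro.

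| Mean dE | Mean dC (euro) | Correlation | P(dominance), any λ | λ = 0 | λ = 5,000 | λ = 20,000 | Gap at 0 | Gap at 20,000 |
|---|---|---|---|---|---|---|---|---|
| 0.12 | 200 | 0 | 0.354 | 0.370 | 0.722 | 0.921 | 0.016 | 0.567 |
| 0.12 | 0 | 0 | 0.480 | 0.499 | 0.802 | 0.942 | 0.019 | 0.462 |
| 0.12 | −200 | 0 | 0.613 | 0.641 | 0.876 | 0.956 | 0.028 | 0.343 |
| 0.12 | 200 | −0.3 | 0.369 | 0.375 | 0.704 | 0.908 | 0.006 | 0.539 |
| 0.05 | 200 | 0 | 0.270 | 0.360 | 0.516 | 0.694 | 0.090 | 0.424 |

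The direction is the same in every row, as the algebra requires. The size moves a good deal with the assumed inputs.

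**The case against.** The strongest reply is that this is a slip of one verb. The sentence names a standard object and gives it its standard axis. If 'dominates' is read loosely, as being preferred at that ceiling, the whole sentence is coherent and describes the usual curve. A flat plot would be noticed, and the next sentence points the analyst to health-economic guidelines. This largely stands as a guess at intent. It does not remove the problem: the guideline sentence gives no formula, and dominance has a settled meaning in this field that the article does not displace.

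A second reply is that a journal article may leave the net-benefit formula to a fuller plan. That is true of an omitted formula. Here, however, the article states what is plotted and states it wrongly.

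A third reply is that the curve is not the only statement of uncertainty. Bootstrap intervals and the scatter on the plane are also promised, and the scatter shows directly how many replicates are more effective but more costly. This stands, and it limits the harm.

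A reader might go further and infer that the trial has chosen a flat curve, so that decision makers will be led to reject a worthwhile intervention. The documents do not support that. They show a wrong word beside the right object and axis, and they contain no cost or recovery difference from which the size of an understatement could be derived.

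**Conclusion.** The point holds as a minor correction. On the standard meaning of dominance, the quantity as worded is constant over the ceilings and is a lower bound on the probability of cost-effectiveness at each non-negative ceiling. That part is exact and rests on no assumption about the data.

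The size for this trial is unknown. The illustrations show only the pattern: little difference near a ceiling of zero, and a growing one when many replicates are more effective but more costly. The Abstract classes economic costs as a secondary outcome. The primary outcomes, the sample size and the data to be collected are untouched. The statement "We will report the incremental cost-effectiveness ratio" and the definition that follows it contain no error on this point.

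**What to change.** In the final part of the Economic analysis section, replace the wording about dominating usual care with wording that the intervention is cost-effective compared with usual care. Define this as the share of the 2,500 bootstrap replicates in which ceiling × difference in effect − difference in cost is above zero, computed at each ceiling. The ceiling should be in the unit of the effect plotted.

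If dominance is also of interest, report the share of replicates in the more effective, less costly quadrant as one separate figure.

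The cost is one sentence. It uses the same bootstrap output and needs no new data.

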## Discussion

The aim of this study is to investigate the effectiveness of an internet-based self-help intervention on depressive and anxiety symptoms in pregnancy. Furthermore we investigate the effects on pregnancy outcome. Through a calculation of costs and quality of life gains an indication can be given on the cost effectiveness of the intervention. This study has several limitations.

First not all women have access to the internet. This might be especially true for those with increased vulnerability for affective symptomatology during pregnancy such as social disadvantaged women in particular those with illiteracy, low educational level and low income. However especially in Western countries internet is broadly available and therefore this intervention is widely accessible during pregnancy.

Second, drop out rate may be high in the non intervention group due to lack of motivation. In order to counter this, therapy is offered at a later stage, 6 weeks post delivery.

A third limitation is the use of self rating instruments only. However since this intervention is aimed at affective symptoms and not at affective disorders a formal diagnosis seems not necessary.

The strength of the study is that we examine a short practical intervention for a specific group with mild to severe affective symptoms, which has proven to be (cost) effective in other populations. The broad inclusion and the use of the internet will allow us to create a high external validity. Furthermore the study is not only aimed at depressive, but also at anxiety symptoms, which is a common, but often neglected symptom in pregnancy and postpartum.

In case effectiveness is proven we will be able to offer an effective treatment of affective symptoms in pregnancy and their complications, reach many women and making therapy easier accessible.

